# Perioperative or adjuvant mFOLFIRINOX for resectable pancreatic cancer (PREOPANC-3): study protocol for a multicenter randomized controlled trial

**DOI:** 10.1186/s12885-023-11141-5

**Published:** 2023-08-07

**Keywords:** Pancreatic cancer, mFOLFIRINOX, Neoadjuvant therapy, Adjuvant therapy, Randomized controlled trial, Overall survival

## Abstract

**Background:**

Surgical resection followed by adjuvant mFOLFIRINOX (5-fluorouracil with leucovorin, irinotecan, and oxaliplatin) is currently the standard of care for patients with resectable pancreatic cancer. The main concern regarding adjuvant chemotherapy is that only half of patients actually receive adjuvant treatment. Neoadjuvant chemotherapy, on the other hand, guarantees early systemic treatment and may increase chemotherapy use and thereby improve overall survival. Furthermore, it may prevent futile surgery in patients with rapidly progressive disease. However, some argue that neoadjuvant therapy delays surgery, which could lead to progression towards unresectable disease and thus offset the potential benefits. Comparison of perioperative (i.e., neoadjuvant and adjuvant) with (only) adjuvant administration of mFOLFIRINOX in a randomized controlled trial (RCT) is needed to determine the optimal approach.

**Methods:**

This multicenter, phase 3, RCT will include 378 patients with resectable pancreatic ductal adenocarcinoma with a WHO performance status of 0 or 1. Patients are recruited from 20 Dutch centers and three centers in Norway and Sweden. Resectable pancreatic cancer is defined as no arterial contact and ≤ 90 degrees venous contact. Patients in the intervention arm are scheduled for 8 cycles of neoadjuvant mFOLFIRINOX followed by surgery and 4 cycles of adjuvant mFOLFIRINOX (2-week cycle of oxaliplatin 85 mg/m^2^, leucovorin 400 mg/m^2^, irinotecan 150 mg/m^2^ at day 1, followed by 46 h continuous infusion of 5-fluorouracil 2400 g/m^2^). Patients in the comparator arm start with surgery followed by 12 cycles of adjuvant mFOLFIRINOX. The primary outcome is overall survival by intention-to-treat. Secondary outcomes include progression-free survival, resection rate, quality of life, adverse events, and surgical complications. To detect a hazard ratio of 0.70 with 80% power, 252 events are needed. The number of events is expected to be reached after the inclusion of 378 patients in 36 months, with analysis planned 18 months after the last patient has been randomized.

**Discussion:**

The multicenter PREOPANC-3 trial compares perioperative mFOLFIRINOX with adjuvant mFOLFIRINOX in patients with resectable pancreatic cancer.

**Trial registration:**

Clinical Trials: NCT04927780. Registered June 16, 2021.

## Introduction

Pancreatic cancer is the fourth leading cause of cancer-related death in Europe and the third in the United States [1, 2]. For patients with resectable pancreatic cancer, surgery followed by adjuvant chemotherapy is currently the standard of care [3, 4]. In 2018, the French-Canadian PRODIGE 24/CCTG PA.6 randomized controlled trial (RCT) showed the superiority of adjuvant mFOLFIRINOX (5-fluorouracil with leucovorin, irinotecan, and oxaliplatin) over adjuvant gemcitabine [5]. Consequently, guidelines recommend adjuvant mFOLFIRINOX for patients with resected pancreatic cancer [3, 4].

The main concern regarding adjuvant chemotherapy is that half of the patients never start adjuvant treatment as a result of surgical complications, clinical deterioration, or early recurrence [6, 7]. Neoadjuvant chemotherapy, on the other hand, guarantees early systemic therapy and may thereby improve overall survival. Furthermore, it may prevent futile surgery in patients with rapidly progressive disease. However, some argue that deterioration during neoadjuvant chemotherapy may preclude surgery and tumors not sensitive to chemotherapy may progress and become unresectable.

Neoadjuvant therapy has been compared with adjuvant therapy in several RCTs for patients with resectable and borderline resectable pancreatic cancer. A recent meta-analysis suggests a survival benefit of neoadjuvant therapy (hazard ratio [HR] 0.66, 95% CI 0.52–0.85; *P* = 0.001) [8]. However, in the subgroup of patients with resectable pancreatic cancer, no statistically significant difference was observed (HR 0.77, 95% CI 0.53–1.12; *P* = 0.18) [8]. Notably, these trials used gemcitabine-based regimens while the current standard of care is adjuvant mFOLFIRINOX [5]. Therefore, an RCT that directly compares neoadjuvant or perioperative to adjuvant administration of mFOLFIRINOX in patients with resectable pancreatic cancer is needed to investigate the optimal approach.

The primary objective of the PREOPANC-3 trial is to investigate whether perioperative mFOLFIRINOX improves overall survival compared with adjuvant mFOLFIRINOX in resectable pancreatic cancer.

## Methods

### Trial design

The PREOPANC-3 trial is an international, multicenter, phase 3, RCT initiated by the Dutch Pancreatic Cancer Group (DPCG). Patients with resectable pancreatic cancer are randomized to neoadjuvant mFOLFIRINOX followed by surgery and adjuvant mFOLFIRINOX (intervention; arm 1) or to surgery and adjuvant mFOLFIRINOX (comparator; arm 2) (Fig. 1). Randomization is performed centrally in a 1:1 ratio using the minimization technique with World Health Organization (WHO) performance status (0 vs. 1), serum carbohydrate antigen 19–9 (CA 19–9) level (< 300 vs. ≥ 300 U/ml), and center as stratification factors.

**Fig. 1 Fig1:**
[figure not shown]
Treatment schedule

### Patients

Eligible patients have cytologically or histologically confirmed non-metastatic, resectable pancreatic ductal adenocarcinoma. Cytological confirmation may include both suspicious (category V) or malignant (category VI) according to the Papanicolaou Society of Cytopathology guidelines [9]. Resectability is determined on computed tomography (CT) imaging. Resectable pancreatic cancer is defined according to the DPCG criteria as no celiac axis, superior mesenteric artery, or common hepatic artery tumor contact and superior mesenteric and/or portal vein tumor contact of 90 degrees or less (Table 1) [10]. The NCCN definition of resectable pancreatic cancer differs from the DPCG definition as it allows for 180 degrees of venous contact [3].

**Table 1 Tab1:** Dutch Pancreatic Cancer Group criteria defining resectability status at diagnosis

	**Celiac axis**	**Superior mesenteric artery**	**Common hepatic artery**	**Superior mesenteric vein / portal vein**
Resectable (all four required)	no contact	no contact	no contact	≤ 90° contact
Borderline Resectable (minimally one required)	≤ 90° contact	≤ 90° contact	≤ 90° contact	> 90–270° contact and no occlusion
Locally Advanced (minimally one required)	contact > 90°	contact > 90°	contact > 90°	contact > 270° or occlusion

Other inclusion criteria are a WHO performance status of 0 or 1 and adequate hematologic (i.e., hemoglobin ≥ 6 mmol/L [9.7 g/dL]; white blood count ≥ 3.0 × 10^9^/L; platelets ≥ 100 × 10^9^/L) and renal function (i.e., eGFR ≥ 40 ml/min), and written informed consent (Table 2).

**Table 2 Tab2:** Eligibility criteria

**Inclusion criteria**
• Histological or cytological confirmation (category V: Suspicious or VI: Malignant) of pancreatic ductal adenocarcinoma • Resectable tumor according to DPCG criteria: no arterial contact and venous contact with the superior mesenteric vein or portal vein of 90 degrees or less • No evidence for metastatic disease • WHO performance status of 0 or 1 • Ability to undergo surgery and mFOLFIRINOX chemotherapy • Leucocytes ≥ 3.0 × 10^9^/L • Platelets ≥ 100 × 10^9^/L • Hemoglobin ≥ 6.0 mmol/L • Renal function: eGFR ≥ 40 ml/min • Age ≥ 18 years • Written informed consent
**Exclusion criteria**
• Prior radiotherapy, chemotherapy, or surgery for pancreatic cancer • Prior chemotherapy precluding mFOLFIRINOX • Previous malignancy (excluding non-melanoma skin cancer, pancreatic neuroendocrine tumor (pNET) < 2 cm, and gastrointestinal stromal tumor (GIST) < 2 cm), unless no evidence of disease and diagnosed more than 3 years before diagnosis of pancreatic cancer, or with a life expectancy of more than 5 years from date of inclusion • Pregnancy or lactation • Serious concomitant systemic disorders that would compromise the safety of the patient or his/her ability to complete the study, at the discretion of the investigator

Exclusion criteria are prior radiotherapy, chemotherapy, or surgery for pancreatic cancer. In addition, patients with a previous malignancy (excluding non-melanoma skin cancer, pancreatic neuroendocrine tumor [pNET] < 2 cm, and gastrointestinal stromal tumor [GIST] < 2 cm) are excluded, unless no evidence of disease and diagnosed more than 3 years before diagnosis of pancreatic cancer, or with a life expectancy of more than 5 years from date of inclusion (Table 2).

Patients with biliary obstruction are eligible, but biliary drainage, preferably using an endoscopically placed self-expanding metal stent, must be performed before the initiation of neoadjuvant therapy if bilirubin is above 25 μmol/L (1.5 mg/dL). Last, all patients must be discussed in a multidisciplinary tumor board meeting before inclusion.

### Treatment

#### Both arms: mFOLFIRINOX

The mFOLFIRINOX regimen consists of oxaliplatin 85 mg/m^2^, leucovorin 400 mg/m^2^, irinotecan 150 mg/m^2^, all at day 1, and 5-fluorouracil continuous intravenous infusion 2400 g/m^2^ over 46 h. The dosages are identical to the regimen used in the PRODIGE 24/CCTG PA.6 trial [5]. Testing of the dihydropyrimidine dehydrogenase (DPD) enzyme prior to initiation of mFOLFIRINOX is mandatory as recommended by the European Medicines Agency [11]. In patients with a (partial) deficiency of the DPD enzyme, 5-fluorouracil dose is adjusted or withheld. Primary prophylaxis with granulocyte colony-stimulating factor (G-CSF) after every cycle of mFOLFIRINOX is recommended.

#### Both arms: surgery

Surgical exploration preferably starts with a staging laparoscopy in the same surgical session. If no distant metastases or unresectable disease is found, patients undergo pancreatectomy, which may include pancreatoduodenectomy, distal pancreatectomy, or total pancreatectomy. Both open and minimally-invasive pancreatectomy techniques are allowed.

#### Intervention arm: perioperative mFOLFIRINOX

Patients in the intervention arm start with 4 cycles of neoadjuvant mFOLFIRINOX. After 4 cycles, restaging is performed with a CT scan and tumor markers CA 19–9 and carcinoembryonic antigen (CEA) to rule out progressive disease. If patients have treatment response or stable disease, patients continue with an additional 4 cycles of mFOLFIRINOX. After 8 cycles, restaging with CT scan and tumor markers is repeated. If there is no evidence of disease progression, patients are scheduled for surgical exploration. After resection, patients receive 4 cycles of adjuvant mFOLFIRINOX, starting within 12 weeks after surgery.

During the neoadjuvant phase, if patients do not tolerate the full 8 cycles despite maximal dose reduction but have no signs of progressive disease, earlier surgical exploration is allowed.

#### Comparator arm: adjuvant mFOLFIRINOX

Patients in the comparator arm start with surgical exploration. After resection, patients are scheduled for 12 cycles of adjuvant mFOLFIRINOX. Evaluation of treatment response using CT scan and tumor markers is performed after 4 and 8 cycles. If the patient is unfit to receive adjuvant mFOLFIRINOX, other adjuvant chemotherapy is allowed to the discretion of the treating oncologist.

### Outcomes

The primary outcome of the trial is overall survival defined as the time between randomization and death from any cause. Secondary outcomes include progression-free survival, number of cycles received, dose intensity, resection rate, quality of life, adverse events, and surgical complications. Progression-free survival is defined as the time between randomization and locoregional progressive disease before or during treatment (resulting in irresectability), the occurrence of distant metastases, recurrent pancreatic cancer after surgery or death from any cause. Adverse events are scored according to the NCI Common Terminology Criteria for Adverse Events (CTCAE), version 5 [12]. Surgical complications are defined according to the Clavien-Dindo classification and the International Study Group on Pancreatic Surgery (ISGPS) definitions [13, 14]. In the intervention arm, pathological response and tumor marker response after neoadjuvant therapy are additional outcomes.

#### Follow-up

Patients are followed for a minimum of five years after randomization using a scheduled follow-up scheme. The first two years, follow-up visits take place every three months and patients undergo chest and abdominal CT scan and tumor marker (CA 19–9 and CEA) evaluation every 6 months. Thereafter, follow-up visits take place every 6 months with CT scan and tumor marker evaluation every 12 months. Patients who discontinue study treatment early will be followed for the primary outcome.

### Data collection and management

Study data will be handled confidentially. Each patient will receive an anonymous identification code. To trace data back to an individual patient, a subject identification code list will be used. Each participating site will safeguard the code list for patients included at their site. The handling of personal data will comply with EU General Data Protection Regulation (GDPR) and the Dutch Act on Implementation of the General Data Protection Regulation. Data will be entered on electronic case report forms using the electronic online database ALEA (FormsVision BV, Abcoude, The Netherlands). Data is entered by a small number of trained data managers that collect data from all study sites.

Quality of life is measured during treatment and follow-up using questionnaires. The PAncreatic CAncer Project (PACAP, www.pacap.nl) collects quality of life forms on all patients with pancreatic cancer in the Netherlands.

### Safety and monitoring

Adverse events grade 3 and higher, according to the NCI CTCAE version 5 definitions, that occur within 30 days of last chemotherapy will be recorded [12]. The local investigator will report serious adverse events (SAEs), defined as an adverse event that resulted in death, was life threatening, or required hospitalization, to the sponsor. Suspected Unexpected Serious Adverse Reactions (SUSARs) are reported to the Medical Ethics Committee and competent authority. A monitor team will monitor the study throughout its duration with visits to the study sites. The visits will be conducted to evaluate the progress of the study, ensure accurate data collection, and check compliance with the study protocol. An independent Data Safety Monitoring Board (DSMB) will be installed to evaluate safety data during the study. The DSMB will meet after the first 100 patients have completed treatment and will investigate the occurrence of deaths and adverse events in both treatment arms.

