
Comparison of survival outcomes of neoadjuvant and adjuvant trials is difficult, if not impossible. Adjuvant trials include only patients who have undergone resection. These patients successfully underwent pancreatectomy and recovered adequately to be considered for adjuvant therapy. In addition, adjuvant trials require a recent CT scan and some trials had upper limits for post-resection CA 19–9. In contrast, neoadjuvant trials include patients with resectable pancreatic cancer on imaging. As a result, neoadjuvant trials include patients that are found to have metastases or unresectable disease at surgical exploration, patients who died from surgery, and patients with surgical complications or clinical deterioration precluding adjuvant therapy. A recent meta-analysis of 7 RCTs demonstrated that even in the upfront surgery arm 1 in 5 patients underwent no resection, mostly due to metastatic disease found during surgery [8].

In the PREOPANC-3 trial, patients in the intervention arm are scheduled for 4 cycles of adjuvant mFOLFIRINOX after 8 cycles of neoadjuvant mFOLFIRINOX and resection. The exact benefit of adjuvant chemotherapy after neoadjuvant FOLFIRINOX and resection is unclear. An international cohort study that investigated the value of adjuvant therapy after neoadjuvant mFOLFIRINOX found improved survival only in the subgroup of patients with pathology proven node-positive disease [25]. We chose 12 cycles of mFOLFIRINOX in both arms to balance the total number of scheduled cycles between the treatment arms.

Radiotherapy is not part of the neoadjuvant treatment in the intervention arm. Currently, there is insufficient evidence that neoadjuvant (chemo)radiotherapy improves overall survival when scheduled in combination with neoadjuvant mFOLFIRINOX. A meta-analysis including 512 patients with resectable and borderline resectable pancreatic cancer treated with radiotherapy after FOLFIRINOX found higher R0 resection rates without improved overall survival [26]. In addition, a propensity matched analysis including 300 patients with borderline resectable pancreatic cancer treated with and without radiotherapy found similar overall survival [27]. The recent phase 2 ALLIANCE A021501 RCT also found no survival benefit of mFOLFIRINOX followed by stereotactic body radiotherapy (SBRT) compared with mFOLFIRINOX alone in patients with borderline resectable pancreatic cancer [21].

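### Grade 3 or higher adverse events are recorded relative to last chemotherapy, so their ascertainment depends on a post-randomization event that differs by arm

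*Protocol article*

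**What the plan says.** Under Safety and monitoring, the protocol article restricts recording of CTCAE version 5 events of grade 3 or higher to those "that occur within 30 days of last chemotherapy will be recorded". This is the only recording window it gives for general adverse events. It states no start, and no alternative anchor such as randomization or surgery.

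Adverse events are an outcome of the trial as a whole. The Outcomes section reads "Secondary outcomes include progression-free survival, number of cycles received, dose intensity, resection rate, quality of life, adverse events, and surgical complications". The data safety monitoring board, meeting after the first 100 patients have completed treatment, "will investigate the occurrence of deaths and adverse events in both treatment arms".

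The order of treatment differs by arm:
- Intervention: "Patients in the intervention arm start with 4 cycles of neoadjuvant mFOLFIRINOX".
- Comparator: "Patients in the comparator arm start with surgical exploration. After resection, patients are scheduled for 12 cycles of adjuvant mFOLFIRINOX". Other adjuvant chemotherapy is permitted for patients unfit for mFOLFIRINOX.

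On how often chemotherapy is never given after upfront surgery, the Introduction says that "half of the patients never start adjuvant treatment as a result of surgical complications, clinical deterioration, or early recurrence". The Discussion cites a meta-analysis in which "even in the upfront surgery arm 1 in 5 patients underwent no resection".

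Two other streams carry safety data. Investigators report serious adverse events (death, threat to life, hospitalization) to the sponsor. Surgical complications are scored by Clavien-Dindo and the ISGPS definitions. Neither is tied to a chemotherapy window in the text.

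**The concern.** Under the rule as written, a patient needs a last-chemotherapy date to have a recording window. In the intervention arm almost everyone has one, because chemotherapy comes first. In the comparator arm a patient has one only after surviving surgery, being resected and recovering well enough to be treated. The article's rationale for the trial is that many patients do not get that far, so the imbalance is foreseeable.

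The intervention arm has a gap of its own. A patient who receives no adjuvant cycles has a window that closes 30 days after the last neoadjuvant cycle, so surgery and recovery may fall partly or wholly outside it.

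What is at stake is the between-arm comparison of a secondary outcome and the safety board's reading of it. The choice of denominator does not repair this. Per randomized patient, someone without a window can count as event-free because nothing was collected. Per chemotherapy-treated patient, nearly a whole arm is set against a subset selected after randomization for recovery and fitness.

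**Working it through.** The article gives no adverse-event rate, so there is no stated figure on this point to reproduce. The calculation below shows how large the loss could be.

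**Inputs from the article**
- Patients per arm: 378 randomized 1:1 (Statistical methods; Trial design), so 378 / 2 = 189.
- Comparator share without chemotherapy, s: 0.20 (not resected, Discussion) to 0.50 (never start adjuvant treatment, Introduction). Both are background figures, not design assumptions.

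**Input assumed**
- r: the risk, in comparator patients without chemotherapy, of a grade 3 or higher event that neither serious-event reporting nor surgical-complication scoring would catch. The article gives no value. Range taken: 0.10 to 0.50.

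**Step 1. Comparator patients without a window = 189 × s**
- 189 × 0.20 = 37.8, about 38
- 189 × 0.50 = 94.5, about 95

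**Step 2. Understatement of the comparator rate per randomized patient = s × r**

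| s | r = 0.10 | r = 0.50 |
|---|---|---|
| 0.20 | 2 points | 10 points |
| 0.50 | 5 points | 25 points |

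**Step 3. Offset from the intervention arm**

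If a share t of intervention patients also loses events at the same risk r, the net distortion is (s − t) × r. With t = 0.10 (assumption):
- smallest: (0.20 − 0.10) × 0.10 = 1 point
- largest: (0.50 − 0.10) × 0.50 = 20 points

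The article does not give the share of intervention patients whose surgery falls outside the window, so t could be smaller or larger than this.

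**Step 4. Primary outcome**

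Overall survival runs from randomization to death and does not use the window. The 252 deaths reproduce by Freedman's formula: (1.960 + 0.842)² × (1.70 / 0.30)² = 7.849 × 32.11 = 252.0. The point does not touch them.

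**The case against.** The strongest reply is that most of what matters clinically is already collected. Fatal and life-threatening events, and those needing hospitalization, are reportable as serious adverse events with no chemotherapy window stated, and surgical complications are a separate outcome. The reasons the article gives for not starting adjuvant treatment are surgical complications, deterioration and early recurrence. The first is scored separately and the other two may lead to serious events. This stands, and it narrows the loss mainly to non-serious, non-surgical events of grade 3 or higher. It does not remove the loss, because Clavien-Dindo and ISGPS are different scales with a different scope and cannot fill a CTCAE comparison between arms.

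The reply also limits three stronger readings that a reader might infer:

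- *Comparator patients without chemotherapy contribute no safety data, so the arms cannot be compared at all.* The serious-event and surgical streams contradict this. The article is also silent on such patients rather than stating that nothing is collected.
- *With a true risk of 50% everywhere, the comparator would show 25% to 40%, a spurious gap of 10 to 25 points.* This gives patients without chemotherapy the same risk as treated patients and then counts all of it as lost, including events caught elsewhere. The article supports neither step.
- *The bias always makes the comparator look safer.* Events missed around surgery in the intervention arm work the other way, and the article does not allow the two to be netted.

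The 20% to 50% range is itself soft. The rule does not specify study chemotherapy, so other adjuvant or palliative treatment might supply an anchor. That would lower the share without a window but make the windows still less alike.

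Finally, the rule may be meant as a chemotherapy-toxicity measure, with its analysis set defined in a document not shown. The article states intention-to-treat for the primary analysis only. However, it lists adverse events as an outcome of the whole trial and has them reviewed in both arms, without labelling them as toxicity among treated patients. Nor is the point merely that detail is missing: the sentence fixes a rule, and that rule operates differently by arm.

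**Conclusion.** The point holds in a limited form. As written, recording of grade 3 or higher adverse events depends on receipt and timing of chemotherapy, which is determined after randomization and differs by arm. About 38 to 95 of 189 comparator patients may have no window, if the article's background figures carry over to this trial. The affected events are mainly those that are neither serious nor surgical.

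The size is unknown. An understatement of about 2 to 25 points in the comparator rate per randomized patient rests on an assumed uncaptured risk of 10% to 50%, and is partly offset by intervention-arm losses. It shows what could happen and is not an estimate of bias. The defect should be corrected because it affects a secondary outcome and the safety board's review. It does not affect the primary analysis.

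**What to change.** Record grade 3 or higher events in all randomized patients, starting at randomization and ending at a point that exists without chemotherapy. One form is the later of 30 days after last chemotherapy and a fixed period after surgery, with a fixed period from randomization for patients who receive neither.

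Compare the arms over one common window from randomization, on the all-randomized denominator. Each patient's recording period must reach at least the end of that window, death or loss to follow-up aside. Label any table restricted to chemotherapy-treated patients as a toxicity summary, not a randomized comparison.

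The cost is a change of protocol wording and extra case report form entries, mainly for comparator patients. A small team of data managers already collects data from all sites, and visits are three-monthly for two years, so prospective collection should be feasible. The article reports 100 patients randomized by January 1, 2023. Whether non-serious events in patients already enrolled can be recovered has to be checked, because nothing in the article shows that they can.
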